#### Subgroup analysis/moderation of treatment effect

The study is not formally powered for subgroup analyses, but we will investigate in an exploratory fashion whether 8-week anxiety (as measured by the GAD-7) intervention effects differ by levels of baseline anxiety, pregnancy complications yes/no at baseline and pre-existing physical health conditions yes/no at baseline. The two-way trial arm by time point interaction terms will be extended to three-way trial arm by time point by baseline subgroup variable terms added to the main analysis model for the primary anxiety outcome (see section “Statistical methods for primary and secondary outcomes {20a}”). If these interaction terms are statistically significant with respect to the subgroup variable of interest, we will present intervention versus control estimates at 8-weeks post-randomisation by baseline anxiety, pregnancy complications, and/or pre-existing physical health conditions levels. This analysis will be clearly stated as exploratory in the primary paper/report and will be interpreted accordingly.

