### Sample size {14}

#### Clinical efficacy sample size

For a two-sided independent samples *t*-test, alpha = 0.05, assuming one baseline and three post-randomisation measures with correlation rho = 0.5 (conservative based on baseline − T2 estimate from Hirsch, Krahe et al., 2021 [27] of rho = 0.42), deflation factor of 0.5 [45], and accounting for 35% attrition (based on online CBT: [46]), we will need 268 participants in total (134 per arm) to have 90% power to detect a GAD-7 effect size of 0.35 (powered slightly conservatively compared to T2 GAD-7 effect size of 0.40 from Hirsch, Krahe et al., 2021 [27]).

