#### Analysis of primary and secondary clinical outcomes

The mean difference in GAD-7 between arms at 8 weeks post-randomisation will be estimated using a mixed-effects linear analysis of covariance (ANCOVA) model with repeated measures and a random intercept at the participant level. We will include as dependent variables the GAD-7 scores at 4 weeks, 8 weeks (primary outcome) and 36 weeks post-randomisation. We will also adjust for trial arm, time, baseline anxiety (GAD-7), weeks of gestation at baseline (a pre-specified baseline variable), the three randomisation stratification variables, and an interaction term for trial arm and time to allow effects to differ over time and be extracted at the different time points. Furthermore, if any baseline variables are found to predict missing outcome data, we will include them as covariates in our model. The mean differences between arms for the GAD-7 at 36 weeks secondary outcome will be estimated using the model described for the primary outcome, with the mean differences between arms for the other secondary outcomes estimated using similar models to those described for the primary outcome.

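### The subgroup question is about 8 weeks, but 8-week subgroup estimates depend on arm-by-time-by-subgroup terms that, as conventionally coded, test change in moderation between visits

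*Protocol article*

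**What the plan says.** All of this is in the protocol article.

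- **Question** (Subgroup analysis/moderation of treatment effect): the aim is to learn "whether 8-week anxiety (as measured by the GAD-7) intervention effects differ by levels of baseline anxiety, pregnancy complications yes/no at baseline", with pre-existing physical health conditions as the third moderator.
- **Model** (same section): the arm-by-time terms of the primary model "will be extended to three-way trial arm by time point by baseline subgroup variable terms added to the main analysis model".
- **Display rule** (same section): "If these interaction terms are statistically significant with respect to the subgroup variable of interest, we will present intervention versus control estimates at 8-weeks". These estimates are to be given separately for each level of the moderator.
- **Status** (same section): "The study is not formally powered for subgroup analyses, but we will investigate in an exploratory fashion".
- **Main model** (Analysis of primary and secondary clinical outcomes): the dependent variables are "GAD-7 scores at 4 weeks, 8 weeks (primary outcome) and 36 weeks post-randomisation". It is a "model with repeated measures and a random intercept at the participant level", and it includes "an interaction term for trial arm and time to allow effects to differ over time and be extracted at the different time points".

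No sentence names an arm-by-subgroup contrast at 8 weeks as the quantity to be tested.

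**The concern.** The question concerns one quantity per moderator: the difference between subgroups in the arm effect at 8 weeks. The rule for showing results refers to a set of terms that spans three visits. In a model with all lower-order terms, a three-way term is a difference between visits in that moderation.

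Two errors become possible. Moderation that is present and stable over time, including at 8 weeks, would rarely meet the condition. Moderation that appears only at 36 weeks, which the Follow-up assessments section places at 12–24 weeks post-birth, could cause 8-week subgroup effects to be displayed when there is no 8-week difference to show. Also, because subgroup-specific estimates appear only after a significant test in an unpowered analysis, those that do appear will on average be exaggerated.

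**Working it through.** **Inputs from the protocol.** Sample size section: 268 randomised (134 per arm), 90% power, effect size 0.35, alpha 0.05, correlation 0.5, deflation factor 0.5, 35% attrition, and a two-sided test ("For a two-sided independent samples" t-test). Allocation is 1:1 (Sequence generation).

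**Assumptions not in the protocol.** A binary moderator with 50% (or 30%) prevalence; moderation of 0.35 to 0.7 SD; equal correlation between all visits.

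**Reproducing the plan's own figure.** The t-based sample size for 0.35 SD is 173 per arm. Then 173 × 0.5 = 86.5, rounded up to 87, and 87 / 0.65 = 133.8, so 134 per arm and 268 in total. This agrees with the protocol. Number analysed: 268 × 0.65 = 174.2. The subgroup analysis has no stated figure of its own.

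**What the terms mean.** Let m4, m8 and m36 be the arm-by-subgroup difference at each visit. With all lower-order terms and 4 weeks as reference:
- arm-by-subgroup term = m4;
- three-way terms = m8 − m4 and m36 − m4;
- quantity asked for = m8 = arm-by-subgroup term + first three-way term.

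If m4 = m8 = m36, both three-way terms are zero whatever the size of the moderation, and the test rejects at its 5% level. This step needs none of the numerical assumptions. It does need the coding and constancy over time.

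**Direct 8-week contrast.** After adjustment for baseline, the variance per visit is 1 − 0.5² = 0.75 and the covariance between visits is 0.5 − 0.5² = 0.25. With a 50/50 subgroup each of the four cells holds 174.2 / 4 = 43.55.
- Var(m8) = 4 × 0.75 / 43.55 = 0.0689; SE = 0.262 SD.
- Power for 0.5 SD = Φ(0.5 / 0.262 − 1.96) = about 48%.
- With a 30/70 split, Var = 3 / (174.2 × 0.21) = 0.0820, SE = 0.286, power 41.5%.

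**Joint test of the two three-way terms.** Var(m8 − m4) = 4 × (2 × 0.75 − 2 × 0.25) / 43.55 = 0.0918, and the two terms correlate at 0.5. If moderation of size d occurs only at 36 weeks, the noncentrality is d² / (0.0918 × 0.75). For d = 0.7 this is 7.11, which on 2 df gives 66% power.

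| Moderation at 4 / 8 / 36 weeks (SD), 50/50 subgroup | Three-way condition met | Direct 8-week contrast significant |
|---|---|---|
| 0.35 / 0.35 / 0.35 | 5% | 27% |
| 0.5 / 0.5 / 0.5 | 5% | 48% |
| 0.7 / 0.7 / 0.7 | 5% | 76% |
| 0.35 / 0.7 / 0.7 | 20% | 76% |
| 0 / 0 / 0.7 | 66% | 5% |

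A simulation with 3,000 replicates agrees. With constant 0.7 SD moderation, the three-way condition was met in 5.6% of trials and the 8-week contrast was significant in 75.4%; in 71.7% the contrast was significant while the condition was not met. With 0.7 SD at 36 weeks only, the condition was met in 65.3%, and in 61.6% it was met with no significant 8-week moderation.

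**The other coding.** Suppose the lower-order arm-by-subgroup term is left out, so that each three-way term is the moderation at one visit. A joint test then has 3 df and noncentrality (43.55 / 4) × m′C⁻¹m, where C has 0.75 on the diagonal and 0.25 elsewhere. For constant 0.5 SD this is 10.89 × 0.25 × 2.4 = 6.53, power about 56%, so stable moderation is no longer missed. For 0.7 SD at 36 weeks only it is 10.89 × 0.49 × 1.6 = 8.54, power about 69%, so the condition is still often met without any 8-week difference.

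**The case against.** The strongest objection is that a condensed sentence is being read as a full specification. The section opens with 8-week effects, ties significance to the subgroup variable of interest, and extends a term whose stated purpose is to let effects be extracted at each visit. It can be read as intending the arm-by-subgroup contrast at 8 weeks. Exact coding and contrasts normally sit in the SAP, which exists but is not shown. This stands as a reason for moderate confidence. It does not dispose of the point, because the protocol states a decision rule, refers to the terms in the plural, and does not single out 8 weeks.

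The 5% figure also requires moderation to be exactly equal at visits running from the end of the intervention to after birth. The protocol gives no reason to expect that, and in the varying pattern above the condition is met in 20%. The 0.5 SD moderator is larger than the whole powered effect of 0.35, and at 0.35 SD even the direct contrast has only 27% power. Baseline anxiety may be analysed as continuous. All of this stands and limits how far the numbers can be pressed.

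Showing stratum estimates only after a significant interaction is a common convention meant to discourage over-reading. A reader might infer that the protocol will suppress the moderation results altogether. It does not say so: it conditions only the arm comparisons by subgroup level, and is silent on whether interaction estimates and p-values will be given.

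**Conclusion.** The point holds in a qualified form. The stated question and the stated condition for display do not match. Under conventional factorial coding the condition tests change in moderation over time: about 5% against 48% for constant 0.5 SD moderation (50/50 subgroup, about 174 analysed, correlation 0.5), and about 66% when 0.7 SD moderation exists only at 36 weeks. Under visit-specific coding the first failure disappears but the second remains if the terms are tested jointly.

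A reader might infer that the protocol certainly tests the wrong hypothesis, or that stable moderation is bound to be missed. The documents do not support that: it depends on coding the article does not state and on moderation being exactly constant, and a benign reading of the sentence is open. Nor does the point touch the primary estimate. The analysis is labelled exploratory and unpowered, and the harm is confined to what is tested and shown about moderators. Confidence is moderate.

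**What to change.** State that the extended model includes the arm-by-subgroup and time-by-subgroup lower-order terms as well as the three-way terms, and that the test for each moderator is the single arm-by-subgroup contrast at 8 weeks. This can be obtained as a linear combination or by making 8 weeks the reference visit. If baseline anxiety is kept continuous, the same contrast is the arm-by-baseline slope at 8 weeks.

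Report that contrast and the subgroup-specific 8-week effects with 95% confidence intervals for all three moderators whatever the p-value, labelled exploratory. If the SAP already specifies this contrast, align the protocol wording with it.

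The cost is about two sentences and one extra table. No new data are needed, and the planned model already allows effects to be extracted by visit.

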### Methods in analysis to handle protocol non-adherence and any statistical methods to handle missing data {20c}

#### Complier average causal effect analysis

We have also specified a Complier Average Causal Effect (CACE) analysis for the 8-week primary GAD-7 outcome to estimate intervention effects in those who completed all 30 trials in a session for at least 10 out of the 12 RELAX sessions. We will use an instrumental variable approach using the stata command `xtivreg` to handle the longitudinal data, and generally include the same covariates used for the main ITT analysis of the primary GAD-7 outcome.

#### Missing data

Where available we will use missing value guidance provided for scales. Where this is not available, we will prorate missing items only when there are no more than 20% missing items by replacing the missing item values with the mean value of the complete items for each individual. Missing baseline data will be simply imputed [52]. Missing outcome data will mainly be dealt with using maximum likelihood methods to fit the mixed models and including baseline variables that predict missing outcome data (to make the missing at random assumption more plausible). We will consider performing multiple imputation for primary and secondary outcomes only if there are post-randomisation variables that are predictive of missingness for these measures, and the proportion of participants with missing values for any of the primary or secondary outcome variables is equal or greater to 10% [53].

### Plans to give access to the full protocol, participant-level data and statistical code {31c}

The datasets generated during and/or analysed during the current study will be stored in the King’s Open Research Data System (KORDS), which is a repository that allows data sets to be shared openly [54].

Any data shared will be pseudonymised final datasets made available following publication of the trial papers, as agreed by the Trial Management Group nearer to the time of the deposit.

The local Research and Development office has reviewed these plans and advised that the participant consent is currently appropriate for this data sharing, i.e. with the participant clause in the consent form: “I understand that the research team may use my data for future research and that my data may be shared anonymously with other researchers”. There are no plans to share the statistical code or full protocol.

## Oversight and monitoring

### Composition of the coordinating centre and trial steering committee {5d}

The RELAX research team (i.e. Trial Coordinator, Research Assistant(s), Research Midwife and trained and supported students/volunteers working on the project) are responsible for the day to day running of the trial and participant contact. This may be to screen potential participants for eligibility, to contact participants as they progress through the RELAX intervention, to prompt participants to complete assessments, to complete post-intervention interviews or deal with queries relating to platform or risk issues. Oversight will be provided by the trial CI (a Clinical Psychologist). The team holds weekly team meetings to discuss any potential participant issues and to share wider trial updates with the CI. The RELAX research team meet monthly with the CI and the broader RELAX Trial Management Group, including NHS site Principal Investigators, statisticians, co-applications to provide broader trial updates and make key decisions.

The RELAX TSC will meet at least yearly to provide broader trial oversight. The TSC consists of trial specialists, statisticians, clinicians and the PPIE Lead for the study and three PPIE representatives, with a Charter of membership developed and signed.

#### Patient and public involvement and engagement

We have worked closely with PPIE representatives from the conception of this research. We will continue to work closely with our PPIE group to ensure that the needs of the ultimate beneficiaries of the research (pregnant women/service users) remain central to the project. Thus, we will ensure that the study:Develops materials pertinent to pregnant women’s day to day concerns,Identifies multiple scenarios that trigger RNT and anxiety in a broad range of pregnant women,Has community and maternity service users’ feedback on proposed adaptations to the intervention and trial plans,Has community and maternity service user advice on ways of engaging with the target audience and maximising participation rates, particularly focusing on issues of diversity and inclusion, andPromotes and develops good practice in PPIE, reporting our methods and learning.

Study findings will be communicated to maternity services, charities, support networks, and community and professional organisations, ensuring that communication messages, language and images are acceptable, relevant and appealing to target audiences and service users from different communities, and informed by the advice of named third sector organisations and advocacy groups (including King’s College Denmark Hill Maternity and Neonatal Voices Partnership (MNVP), Maternal Mental Health Alliance, National Maternity Voices). We will hold an online learning event, write a blog for public and professional health service audiences, and use social media to share and discuss the findings. Further information is publicly available at the NIHR Applied Research Collaboration (ARC) South London website [55].

### Composition of the data monitoring committee, its role and reporting structure {21a}

The RELAX DMEC is set up to be an advisory group to the TSC. As there is no planned interim analysis, the DMEC will monitor the trial and communicate any concerns to the TSC, who can decide to terminate the trial prematurely if necessary. The DMEC consist of trial specialists, statisticians and clinicians, and a Charter of membership has been developed and signed.

### Adverse event reporting and harms {22}

All adverse events and serious adverse events (SAE) for participants (and their infants) will be recorded on the RELAX platform. Clinical symptoms will be documented and accompanied with a simple, brief description of the event, including dates as appropriate, as well as an assessment of the event’s severity and relatedness to the intervention, initially completed by the researcher and signed off by the CI. If it is in the best interest of the participant or clinical team managing a participant’s maternity care, the study team will inform the clinical team of any AEs that a participant experiences. For participants linked to one of the four participating NHS sites, this will be done promptly (usually on the same day), where the site PI will have access to review the event details on the platform researcher’s interface. SAE and adverse device effects will be reported to the sponsor within 24 h of the researcher becoming aware of the event. Relevant regulatory authorities and the platform manufacturer will also be made aware of the event. The trial protocol includes a detailed list of expected pregnancy-related SAEs, e.g. hospital admission for active labour, that are documented but exempt from the same level of sponsor and regulatory authority reporting.

### Frequency and plans for auditing trial conduct {23}

The investigators and the institutions will permit trial-related monitoring, audits, REC review and regulatory inspections (where appropriate) by providing direct access to source data and other relevant documents.

### Plans for communicating important protocol amendments to relevant parties (e.G. Trial participants, ethical committees) {25}

In the event of any amendments, the Sponsor’s Research and Development office and regulatory ethics boards will be notified. In addition, where appropriate, the MHRA will also be informed. Prior consultation will be undertaken with trial PPIE, TMG, TSC and DMEC committees, as appropriate, as well as with the funder (NIHR).

### Dissemination plans {31a}

The planned dissemination route is to further develop a sustainable model for RELAX. This will cover updates to software, materials and technical support (OS updates and upgrades), as well as web-platform hosting. RELAX could potentially be licenced for use by NHS services and third sector organisations who support pregnant women. Implementation plans could be assessed during a subsequent effectiveness trial.

We will send all participants a summary of the study findings using lay language after data analysis has been completed. We will present the study findings at conferences, hold dissemination workshops for stakeholders and our participating NHS sites. We will also produce policy lab briefings, working together with the KCL Policy Institute and our PPIE group.

We will produce a publication on the role, practice and impact of PPIE in the study, publish trial data in high-impact journals and publicise our findings via social and published media to disseminate the clinical results to a broader audience. Our PPIE group will work with us to develop the dissemination plan.

## Discussion

The RELAX Study is a parallel two-arm randomised controlled trial testing an online interpretation training intervention to evaluate whether at-risk pregnant women who complete RELAX alongside usual care report less perinatal anxiety before and after birth than those who receive usual care only. RELAX is based on an evidence-based intervention previously shown to reduce anxiety in non-pregnant populations [25–27], which we have adapted and tailored for a pregnant sample. Specifically, it is designed for pregnant women who experience high levels of RNT, an established risk factor for later anxiety. On the basis that RNT is maintained by a negative interpretation bias, RELAX aims to reduce the tendency to make negative interpretations (i.e. the theorised mechanism of the intervention) in order to reduce RNT, in turn resulting in lower levels of anxiety symptoms. To our knowledge, RELAX is the only pregnancy-tailored online intervention specifically aimed at targeting RNT.

This research addresses the need for targeted early interventions for perinatal anxiety, which feature in the NHS Long Term Plan. It is well-established in non-perinatal populations that interventions which target individuals who are identified as being at-risk of psychological problems are more effective than non-targeted universal approaches [56]. Accordingly, the development of a low-intensity (self-help), highly accessible, cost-effective intervention to address perinatal anxiety is an exciting prospect.

We have included PPIE contributors with lived experience of perinatal anxiety in the design and development of the trial. Our PPIE members have indicated that interventions for perinatal anxiety delivered online would be a feasible and welcomed way to engage at-risk pregnant women. This population typically has multiple responsibilities, rendering a home-based intervention that can be completed at a time convenient for them as having great appeal. The PPIE members have also been involved in the development of the scenarios used in the intervention, alongside contributing to the bespoke RELAX platform design and testing the platform during the usability testing phase, thus ensuring that the intervention platform was built, tested and endorsed by the intended service user group. The trial team involves experts and clinicians from psychology, midwifery and biostatistics, as well as an expert PPIE researcher. Each team member brings their unique perspectives to the project, leading to meaningful muti-disciplinary research and effective public involvement from a broad and highly motivated group.

In sum, this trial will establish whether an intervention for pregnant women with high levels of RNT that does not require delivery by a mental health specialist can prevent escalating anxiety in the perinatal period. Should the trial demonstrate that RELAX is efficacious, an effectiveness trial to aid implementation could be conducted. Moreover, evidence of efficacy has the potential to open other avenues for future research, e.g. investigations of whether there are longer-term, sustained positive impacts of the intervention post birth (i.e. in the “fourth” trimester), when the additional changes, challenges and worries of motherhood become apparent. In addition to scaling up the intervention for use in pregnancy, there is scope for it to be translated into languages other than English, and developed for other groups, such as partners of pregnant women and birthing people, and pregnant women who already report high levels of anxiety and/ or psychiatric diagnoses.

